### 2.2. Phase II: The Pilot Study and the Qualitative Process Evaluation

Study design of the pilot study

In phase II, the newly developed intervention protocol’s feasibility and acceptability will be tested using a pre-post pilot study incorporating a qualitative process evaluation.

(1)Pilot study: Study sample

The inclusion criteria will be female patients (1) aged 18 years or older; (2) confirmed diagnosis of breast cancer at stage I, II, or IIIa; (3) confirmed diagnosis of CVDs, such as heart failure, hypertension, coronary artery disease, cerebrovascular accidents (e.g., stroke, transient ischemic attack), cardiomyopathy and arrhythmias; (4) able to read, write, and communicate in English; (5) have completed active anticancer treatment including chemotherapy and radiotherapy, and are receiving regular healthcare in primary care centre from GP/practice nurses; (6) willing to participate in the research study and provide informed consent. The exclusion criteria: patients with unstable health conditions with mental health issues or critically ill patients unable to participate in physical activities (e.g., suffering from life-threatening diseases, extremely weak), cognitive impairment, currently involved in another research study, or scheduled anticancer treatment during the study period.

(2)Sample size and study settings

Based on the rule of thumb suggested by Julious [60], a sample size of 12 will be employed in this pilot single-group pre-post study. When taking into account a 20% dropout rate based on a clinical study by Cramer et al. [61], 15 participants will be recruited for this study.

(3)Study procedure

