#### 2.2.1. Outcomes and Measurements

The study will employ a demographic data sheet that has been specifically developed by the research team to gather information on the socio-demographic characteristics of the patients, such as age, height, race/ethnicity, as well as their medical history, such as date of BC and CVD diagnosis, the current stage of BC, the type and date of BC and CVD treatment.

(1)Primary outcomes

The primary outcomes will be the feasibility, acceptability and safety outcomes. The feasibility outcome will measure the feasibility of the questionnaires, recruitment and the intervention delivery. The acceptability of the intervention will be assessed by assessing the acceptability among the participants. The safety of the intervention will be measured by the safe delivery of the intervention. The primary outcome will also measure the recruitment, retention, and dropout and will be evaluated as the fundamental aim.

The recruitment rate is the percentage of eligible participants who consented to participate in the study.The retention rate will measure the percentage of participants who remain in the study throughout the entire study period, from enrolment to follow-up (week 12).The dropout rate will be calculated based on the percentage of participants withdrawn from the study after enrolment.The feasibility of the questionnaires will be assessed by measuring the percentage of missing responses for each item and the entire scale.The feasibility of the recruitment will be assessed by measuring the number of weeks or months needed to achieve the target number of sample size.The adherence rate to the NGPS protocol will measure the percentage of participants who followed the interventions as intended. This will measure the feasibility and acceptability of the study intervention.The safety of the intervention includes discomfort or adverse effects related to NGPS intervention by keeping a daily logbook and reporting via telephone or face-to-face.Acceptability will assess the participant’s satisfaction, benefits received and obstacles faced using an investigator-created questionnaire.

(2)Secondary outcomes

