#### 2.2.2. Data Analysis of the Pilot Study

Data will be analysed using descriptive and exploratory inferential statistics using SPSS 26.0 with the intention of feasibility assessment and not for formal hypothesis testing [70]. In a single-group pre-post-test study, the characteristics of the sample will be summarised using descriptive statistics such as frequency counts, percentages, means, and standard deviations. The descriptive data analysis can give an overview of the sample’s age, gender, ethnicity, education level, income, breast cancer treatments, and other demographic variables.

The feasibility outcomes of the study such as recruitment, follow-up assessments, and questionnaire/intervention acceptability will be determined using descriptive data [71]. Mean and standard deviation will be used to analyse interval and ratio data, such as the time taken for participant recruitment and the average time and frequency of physical activity [71]. The acceptability of the questionnaires will be determined by calculating the proportion of missing data [71]. The feedback on the intervention is measured by assessing the participants’ satisfaction scores. Any adverse events related to physical activity, such as musculoskeletal aches and pain, dizziness, and falls, will be presented as the absolute number of events and the total percentage.

Secondary clinical and behavioural outcomes will be presented descriptively at each assessment point to evaluate the feasibility outcomes for future randomization [70]. Changes over time will be explored using non-parametric methods, given the small sample size and single-group pre–post design [71,72]. The Friedman test will be conducted for continuous variables to correlate the data at three different time points [73]. Cochran’s Q test will be utilised for categorical variables to assess changes in proportions between the pre-test and post-test assessments [74]. These analyses will be exploratory only and will not be interpreted as formal hypothesis tests. Analyses will be conducted using available data from participants who complete each assessment. The extent and reasons for missing data will be reported. Participant attrition will be monitored throughout the study, and differences between completers and non-completers will be examined to evaluate potential attrition bias. No imputation of missing data is planned due to the small sample size and feasibility focus of this study.

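### Questionnaire acceptability, a primary outcome, is summarised among responders only and may be overstated; a comparison of about 12 completers with 3 non-completers cannot rule that out

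*Protocol article*

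**What the plan says.** Section 2.2.1 of the protocol article names acceptability as a primary outcome. One part is a questionnaire covering "satisfaction, benefits received and obstacles faced using an investigator-created questionnaire"; section 2.2.2 adds that feedback on the intervention is summarised through satisfaction scores. A second source is adherence: "The adherence rate to the NGPS protocol will measure the percentage of participants who followed the interventions as intended", which section 2.2.1 links to both feasibility and acceptability.

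Section 2.2.2 sets the rule for missing data: "Analyses will be conducted using available data from participants who complete each assessment", and "No imputation of missing data is planned due to the small sample size and feasibility focus of this study". It also promises to report how much is missing and why. The comparison it offers on attrition is that "differences between completers and non-completers will be examined to evaluate potential attrition bias". No method or threshold is attached to it.

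Section 2.2 schedules data collection at baseline, week 4 and week 12, and section 2.2.3 says that data are gathered at those times. The article does not say when the acceptability questionnaire is given, and describes no collection from a participant who withdraws.

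On numbers, section 2.2 states that "a sample size of 12 will be employed in this pilot single-group pre-post study" and, allowing for 20% dropout, that "15 participants will be recruited for this study".

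**The concern.** For blood pressure or weight, analysing whatever was observed is an acceptable choice in a small pilot. Acceptability is different, because leaving can itself be a sign of poor acceptability. Someone who stops because the programme does not suit them may leave no satisfaction score, so whether the score is missing may depend on what it would have been. A summary among responders would then look better than the view of everyone enrolled, and the gap would be widest when the programme is least acceptable.

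The article gives the completer comparison the task of evaluating attrition bias. With about three people on one side, it can say very little. The acceptability estimate is one of the feasibility parameters meant to inform a later randomised trial, so its denominator should be clear.

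**Working it through.** **Inputs.** Target of 12, dropout of 20% and 15 recruited, all from section 2.2. The article gives no acceptability result, so the counts of favourable answers below are assumptions. So is the reduction of a satisfaction score to favourable or not, since the article defines no cut-off. The two-sided 5% level in step 3 is also assumed, for illustration only.

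**Step 1: the plan's own figure.** 12 / (1 − 0.20) = 15, which reproduces the number recruited. Expected non-completers are 15 × 0.20 = 3, so the expected split is 12 and 3.

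**Step 2: what a respondent-only figure can hide.** Suppose 3 of 15 have no questionnaire and s of the 12 responders are favourable. The respondent-only figure is s/12. Over all enrolled, the worst case is s/15 and the best case is (s + 3)/15.

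| s | Respondents only | Worst case, all 15 | Best case, all 15 |
|---|---|---|---|
| 12 | 100% | 80% | 100% |
| 11 | 92% | 73% | 93% |
| 10 | 83% | 67% | 87% |
| 9 | 75% | 60% | 80% |

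The largest overstatement is s/12 − s/15 = s/60. The largest understatement is (s + 3)/15 − s/12 = (12 − s)/60. At s = 10 these are 10/60 = 17 points and 2/60 = 3 points. When most responders are favourable, the possible error is therefore mainly upward.

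For a mean satisfaction score, the respondent-only mean exceeds the all-enrolled mean by 0.20 × (completer mean − non-completer mean). If non-completers would have scored 1 SD lower, that is 0.2 SD.

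Sampling error is also large: the exact 95% interval for 10/12 is 52% to 98%. Unlike sampling error, selective loss can shift the estimate systematically.

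**Step 3: what 12 versus 3 can show.** The half-width of a 95% confidence interval for a mean difference, in SD units, is t(0.975; 13 df) × √(1/12 + 1/3) = 2.16 × 0.6455 = 1.39. An observed difference of zero would be compatible with true differences of up to about 1.4 SD either way.

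If a t-test were used, power would be 11% for a 0.5 SD difference, 21% for 0.8 SD, 30% for 1 SD and 58% for 1.5 SD; 80% power needs about 1.96 SD. For a binary characteristic, Fisher's exact test has about 30% power for 80% versus 30%, and 43% for 20% versus 80%.

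**The case against.** The case on the other side is substantial, and several parts of it stand.

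- **Acceptability does not come from completers alone.** A reader might infer that it does. But adherence is named as an acceptability measure, and sections 2.2 and 2.3 invite all participants to interview, not only completers. Retention and dropout are primary outcomes in their own right, and reasons for missing data will be reported. The concern is limited to the questionnaire.
- **Adherence is not restricted to those still present.** It is defined as a percentage of participants. A narrower denominator is a possible reading, but the article does not state it.
- **Twelve need not be the questionnaire denominator.** The rule refers to each assessment, not to study completion. The intervention ends at week 4 and follow-up at week 12, so someone lost in between may already have answered. The 12 and 3 split is a scenario at the planned dropout.
- **Overstatement is not established.** The direction depends on people not observed; in the example above, a small understatement is also possible. A fall from 92% to 73% is the worst case for an assumed 11 of 12, not an expected result.
- **No test is planned, and no misreading is announced.** Section 2.2.2 says the analysis is not for formal hypothesis testing, and nowhere says that an absence of difference will be taken as absence of bias. It would go too far to say that the check gives false reassurance. The confidence interval in step 3 shows the limited information whether or not a test is run.
- **The available-data sentence sits in a paragraph that opens with secondary outcomes.** This is fair, but it refers to analyses without restriction, is followed by general statements on missing data and attrition, and no other rule is given for the primary outcomes.
- **An article may leave questionnaire timing and withdrawal procedures to the full protocol.** Agreed, and their absence alone is no finding. The point rests on the rule and the comparison that the article does state.
- **Little depends on the figure.** The Discussion says that no progression criteria were set in advance and treats the results as preliminary. This limits the consequence, but an estimate intended for a later trial still needs a clear denominator.

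**Conclusion.** The point holds in a limited form. Under the stated rule, the questionnaire part of acceptability would be summarised among those who answer, and may be overstated if dissatisfied participants leave. With 3 of 15 missing and 10 of 12 favourable, the all-enrolled figure lies between 67% and 87% against a reported 83%. The most that 3 missing could add is 20 points, when all 12 responders are favourable. A comparison of about 12 with 3 cannot exclude differences of around 1.4 SD, so it should not support a conclusion that attrition bias is absent.

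This rests on three assumptions: that the available-data rule covers the questionnaire, that those who withdraw are not asked to complete it, and that about 3 of 15 are missing at that assessment. With fewer missing, the gap shrinks. The improvement is worth making because it is cheap and concerns a primary outcome, but it does not undermine the pilot.

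**What to change.** 1. Offer the existing acceptability questionnaire to any participant who withdraws, at the time of withdrawal.
2. Report the respondent-only acceptability result beside the number enrolled, with best- and worst-case bounds over all enrolled. Keep the worst case as a bound, not the main analysis: no cut-off for satisfied is defined, and someone may leave for reasons unrelated to the programme. For a score, the bounds can use the lowest and highest possible values.
3. State that adherence uses all enrolled participants as its denominator.
4. List each non-completer's baseline values, last session attended and reason for leaving. Present any comparison with completers descriptively, and state that it cannot be used to conclude that there is no attrition bias.

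The cost is some wording, one extra questionnaire handout at withdrawal, and a wider, less favourable acceptability range in the report.

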#### 2.2.3. Quality Assurance and Intervention Fidelity

To ensure the quality assurance of the pilot study, the primary researcher will create standard operating procedures for all study procedures, including recruitment and data collection. Participant recruitment will be conducted using inclusion and exclusion criteria, following recruitment procedures detailed in the study protocol, and all recruitment activities will be documented, monitored, and reported at the biweekly research meetings. Data collection will be conducted by the primary researcher who is completely aware of the data collection procedures to ensure standardisation, and the data will be collected at the time points mentioned to ensure quality.

To ensure intervention fidelity, interventions from an intervention strategy pool (the intervention strategy pool will be developed and validated after the qualitative interviews) will be used for standardisation and to avoid variability in the delivery. The researchers will maintain a study activity log, including intervention delivery and any deviations from the protocol. These details will be reported at the biweekly research meetings. Any decisions on altering the study protocol will be discussed between the researchers and a letter of variation will be submitted to the University of Southern Queensland Human Research Ethics Committee, stating the changes and obtaining final approval. Additionally, the primary researcher will obtain feedback from the patients and the healthcare providers through qualitative process evaluation (as described in Section 2.3) on various components of the NGPS intervention such as relevance, accuracy and wording of the intervention protocol to ensure all components are delivered as intended.

### 2.3. Qualitative Process Evaluation of the Pilot Study

To understand the interventions’ strengths and weaknesses, a qualitative process evaluation will be conducted with both patients and healthcare professionals.

This qualitative study will invite all patients and healthcare professionals who participated in the NGPS intervention. The consented participants will be contacted to schedule an interview at a mutually convenient time after the pilot study. Participants will be given the option to choose between a face-to-face interview, a telephone interview or a video meeting, based on their preference. The doctoral researcher will use a semi-structured interview guide, and the interview will be audio recorded and will involve taking field notes. Before obtaining written consent, a brief explanation of the study will be provided and the participants will be reminded that participation is voluntary and they can withdraw from the study at any time. Data analysis and quality assurance will be the same as in the phase I qualitative study.

## 3. Discussion

In this study, the adoption of the MRC framework and co-design framework as guiding frameworks will provide significant methodological strength. The use of the MRC framework provides a structured and evidence-based approach for developing and piloting the NGPS intervention. It will ensure the intervention is grounded in existing evidence and theories to strengthen the methodological rigour and be suitable for real-world implementation. At the same time the integration of the co-design framework provides meaningful engagement of stakeholders such as BCSs with CVDs and primary healthcare professionals. Incorporating stakeholder involvement in complex health intervention design enhances the acceptability and potential effectiveness of the interventions [75,76]. A user-centred design emphasises the needs and interests of end-users, which will increase the use of research results [77]. Together this will strengthen the overall credibility and practical value of the study, ensuring that the intervention is both evidence-based and patient-centred. The research team also considers the potential challenges in the study. The willingness of stakeholders to contribute to the intervention design and testing can be a potential implementation challenge. Additionally, the study’s settings in primary care and limited resources to develop culturally sensitive or multilingual materials may be challenging factors in the inclusivity of the interventions.

Cardiovascular diseases are underexplored despite the growing evidence that BCSs are at high risk for CVDs due to the cardiotoxic effects of the BC treatment as well as the overlapping risk factors between breast cancer and CVDs. Even though cardio-oncology and survivorship programmes exist, they are not addressing the needs and challenges of BCSs with CVDs due to poor coordination between cardiology and oncology and the absence of shared care models [13,28]. This study will contribute by codesigning self-management non-pharmacological interventions for BCSs with CVDs by integrating the latest evidence, theories, and practice standards. The stakeholder involvement in this study will improve the intervention quality by ensuring that content, delivery methods and intervention strategies reflect the experiences and priorities of intended users [78]. Exploring the feasibility and acceptability of the NGPS intervention in primary care settings may inform survivorship care guidelines and will provide primary healthcare professionals such as nurses, GPs, and allied health professionals with evidence-based tools that will promote long-term health outcomes for patients with both BC and CVDs.

This study has several limitations. The study will be conducted in a specific context within the Australian primary care setting, which could limit the generalisability of the results to other settings. Although multiple recruitment channels (e.g., GP referral, primary clinics and social media platforms) will be used to recruit participants in this study, the use of convenience sampling may introduce selection bias, and the findings may not represent the experience and perspectives of all individuals within the target population, limiting the transferability of the results to other settings. No formal sample size calculation was undertaken to test the hypothesis regarding acceptable recruitment and retention rates, as progression criteria were not pre-specified. Instead, the study was exploratory in nature and aimed to estimate the feasibility parameters. The findings will be interpreted as preliminary and descriptive rather than hypothesis-driven. Future studies should incorporate predefined progression criteria and associated hypothesis testing to enable more robust evaluation of recruitment and retention outcomes. This study uses a single-group pre-post-test with a small sample size; hence, the study cannot determine the efficacy of the self-management interventions. Next, the eight-week post-intervention follow-up might be short in duration; however, the primary aim of the study is to assess the feasibility of the intervention and data collection procedures before conducting a future RCT with a longer follow-up. Additionally, it would be challenging to achieve enduring behaviour change among BCSs even though an eight-week follow-up will be conducted as self-management lifestyle interventions require ongoing commitments and lifestyle modifications that may be challenging to maintain. To enhance adherence beyond the scheduled intervention period, future studies can consider including self-monitoring tools, digital reminders, and peer-support mechanisms. Additionally, strategies such as promoting habit formation by linking the desired behaviour to existing daily routines, enhancing intrinsic motivation by placing focus on personal goals, and values rather than external rewards.

## 4. Conclusions

Overall, this proposed study has the potential to lay the groundwork for self-management interventions for BCSs with CVDs, ultimately enhancing long-term survivorship outcomes, lowering healthcare costs, and serving as a tool for primary healthcare.

## Figures and Tables

**Figure 1 nursrep-16-00253-f001:**
[figure not shown]
Overall research design.

**Table 1 nursrep-16-00253-t001:** Self-management non-pharmacological interventions for CVDs.

Condition	Non-Pharmacological Interventions
CVDs	Diet, physical activity, smoking cessation and weight management
Coronary heart disease	Diet, physical activity, smoking cessation and weight management
Heart failure	Diet and physical activity
Atrial fibrillation	Weight loss and exercise recommended to avoid intensive endurance training
Stroke	Diet, physical activity, smoking cessation, weight management and decreased alcohol consumption and mental health interventions such as mind–body exercise such as taichi, yoga and qigong for mental health management
Peripheral artery disease	Physical activity and smoking cessation
Hypertrophic cardiomyopathy	Moderate to low degree recreational activity and achieve or maintain weight loss for obese individuals

The information presented in this table was adapted from the systematic review [35].

**Table 2 nursrep-16-00253-t002:** Self-management non-pharmacological interventions for BCSs.

Condition	Non-Pharmacological Interventions
Anxiety, depression and distress	Meditation, massage therapy, passive music therapy and hypnosis. Self-administered cognitive behavioural stress management for the management of anxiety and progressive muscle relaxation, guided imagery, visualisation techniques, and autogenic training) for depression management
Fatigue	Physical activity, yoga and hypnosis
Pain	Physical therapy, music therapy post-surgery and hypnosis
Breast cancer-related lymphedema	Progressive resistance training, aerobic exercises, aquatic exercises, self-massage, diaphragmatic breathing and weight reduction
Nausea and vomiting	Self-acupressure and relaxation
Neuropathy	Physical activity
Sleep improvement	Yoga
Vasomotor/hot flushes	Physical activity
Quality of life improvement	Regular exercise or sports, meditation, yoga and hypnosis
Reduction in risk of recurrence	Physical activity, exercise and weight management
Health promotion	Weight management, physical activity, nutrition, alcohol limitation, and smoking cessation

The information presented in this table was adapted from the systematic review [34].

**Table 3 nursrep-16-00253-t003:** A preliminary NGPS intervention protocol.

W1 Initial nurse-led consultation	Format: in-person Time: 15–30 min Health professionals: nurse, and involve allied health professionals if needed Patients: patient and caregiver	Assess the breast cancer survivors’ knowledge of their cardiac conditions and breast cancer, evaluate health literacy, access to resources and motivation to manage their health condition by using the COM-B model. Using the COM-B model, identify the patients’ needs, preferences, and goals and the factors influencing self-management by evaluating their capability, opportunity and motivation to manage their health effectively. Select suitable intervention strategies from the “intervention strategy pool” and develop personalised care plans based on identified factors and a multidisciplinary approach using the COM-B model.
W1 Self-management session	In-person 45–60 min Nurse, patient, and caregiver Involve GP and allied health professionals if needed	Further detail the overall care plan and teach and/or demonstrate the selected suitable intervention strategies to support the behaviour change in patients and evaluate patients to ensure they have mastered the skills for optimal outcomes. Enhance the patient’s capability by providing an education booklet that promotes explicit understanding and engagement in self-management behaviours.
W2 Telehealth with nurse	Telehealth or in-person 15–30 min Nurse and patient	Nurse-led weekly telehealth support sessions using the COM-B model Monitor progress and the appropriateness of the implemented intervention strategies such as frequency and duration to ensure they effectively support the behaviour change. Provide guidance and support to enhance the patient’s capability. Reassess and adjust the care plan based on ongoing assessments to ensure optimal outcomes. Reinforce behaviour change techniques to enhance motivation. Instruct patients to report any healthcare usage during the intervention to maintain accurate monitoring. Encourage patients to ask questions and seek clarification to improve understanding and engagement.
W3 Telehealth with nurse	Telehealth or in-person 15–30 min nurse, patient, and caregiver	Nurse-consultation Medical evaluation. Address any medical concerns via coordination with the multidisciplinary team (including GP and allied health if needed). Review and update the care plan as needed. Check whether all the intervention strategies were correctly implemented. Nurse-led weekly telehealth support sessions (content the same as week 2).
W4 Telehealth with nurse	Telehealth or in-person 15–30 min Nurse, patient, and caregiver	Nurse-led weekly telehealth support sessions using the COM-B model (contents the same as week 2)

